Study phase 2b will consist of subsequent validation of the Australian diabetes-specific QoL questionnaire using the MOS SF-36, the DQOL, and the PAID-20 questionnaires. Three months after study subphase 2a is completed, study subphase 2b will commence. Participants from study subphase 2a will be invited by email to complete the same online questionnaire for a second time. In addition, they will be asked to complete the MOS SF-36 [52], DQOL [49], and the PAID-20 [53] questionnaires. Responses will be analyzed to determine the statistical reliability and validity of the Australian diabetes-specific QOL questionnaire. In all, 100 adults (≥18 years old) with T1DM will be included. Data will be collected via an online questionnaire (estimated completion time 15-18 minutes). Participants will have access to the questionnaire for 2 weeks. If the questionnaire link expires, the participant may request a new link by contacting JP. The data collection period for this phase will last 3 months.

#### Study Phase 3

Study phase 3 will comprise preintervention, intervention, and postintervention procedures. The overall aim of this phase is to determine if an association exists between a low carbohydrate diet, QoL, and glycemic control in adults living with T1DM through use of a cross-sectional cohort study. In all, 16-23 adults (≥18 years old) with T1DM will be included.

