Participants will continue with their usual, daily routine; however, they will commence recording food and fluid consumption in a food diary. Participants will be required to complete the daily food diary 1 week prior to commencing the intervention and for the 12 weeks of the intervention. The participant will email this information to the diabetes dietitian weekly to ensure these records are being maintained, as the information will be used in the final data analysis stage. Participants’ individualized meal plans will be emailed to each participant the day prior to commencing the intervention. Each participant will also be provided with digital kitchen scales and measuring cups and spoons to assist with weighing and measuring foods and fluids to ensure accuracy of quantities consumed. These instruments have been supplied by the GCHHS Study, Education and Research Trust Account (SERTA).

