### Intervention Procedure

All participants will follow a prescribed meal plan to meet their estimated energy needs as per the Schofield formula [64]. Meal plan macronutrient distribution will be 20% carbohydrate, 25% protein, and 55% fat based on the Australian book, *The CSIRO Low Carb Diet* [65]. The meal plan contains no more than 100 g per day of dietary carbohydrate, making this intervention a low carbohydrate dietary regimen according to Feinman et al’s [16] 2015 definition. Alcohol influences blood glucose levels, food and fluid choices, and quantities consumed [66]. For this reason, participants will be strongly advised to abstain from alcohol consumption during the 12-week intervention. Weekly telephone follow-up will be conducted by JP to discuss any concerns or questions participants may have. Follow-up by telephone has been shown to be an effective method to monitor medical nutrition therapy [67,68]. Weekly telephone appointments will also be conducted by the research teams’ endocrinologist (PD) to discuss blood glucose level management and adjust insulin doses as needed.

Any hypoglycemia treatment will be recorded in the food diary and will detail when, what, and how much carbohydrate was used to treat the hypoglycemic event. If any hypoglycemic events occur, PD will discuss this with the participant during the weekly telephone appointment and advice will be provided to avoid future occurrences. Participants will check blood ketones once a week on the morning after an overnight fast to avoid diabetic ketoacidosis. If blood ketones are present (>0.6 mmol/l), participants will follow a “sick day” management plan, and, if unsure what to do, will contact PD for advice. Participants will be encouraged to follow their usual exercise habits, as no exercise advice will be given [69]. This study is unique, and if a participant feels they are unable to complete the 12-week intervention, they may withdraw at any time.

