### Statistical Plan

Table 4 outlines a brief summary of the study objectives, the independent and dependent variables relating to each objective, and the planned statistical analyses to be conducted.

**Table 4 table4:** Brief statistical plan.

Statistical objectives	Independent variable	Dependent variable	Statistical analysis
To develop and pilot the Australian diabetes-specific quality of life questionnaire	Australian diabetes-specific quality of life questionnaire	N/A^a^	Transcribe, code, and identify common themes in the interview data
To validate the Australian diabetes-specific quality of life questionnaire (study developed)	Australian diabetes-specific quality of life questionnaire	Factorial validation indicators: root mean square error of approximation, comparative fit index, and Tucker-Lewis index	Exploratory factor analysis, confirmatory factor analysis, and structural equation modelling
To examine the association between a low carbohydrate diet and glycemic control	Low carbohydrate diet	Glycemic control	Bivariate: ANOVA^b^ and correlations. Multivariate: hierarchical regression controlling for sociodemographic covariates.
To examine the association between quality of life and a low carbohydrate diet	Low carbohydrate diet	Quality of life	Bivariate: ANOVA and correlations. Multivariate: hierarchical regression controlling for sociodemographic covariates.
To investigate whether a low carbohydrate diet mediates the relationship between quality of life and glycemic control	Low carbohydrate diet	Glycemic control and quality of life	Bivariate: ANOVA and correlations. Multivariate: hierarchical regression controlling for sociodemographic covariates.

^a^N/A: not applicable

^b^ANOVA: analysis of variance

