## Discussion

This study is the first of its kind to examine the association between a low carbohydrate diet, QoL, and glycemic control. This cross-sectional study protocol aims to develop, pilot, and validate a diabetes-specific QoL questionnaire and determine if an association exists between QoL and glycemic control while using a low carbohydrate dietary intervention in Australian adults living with T1DM.

The strengths of this study are that, to our knowledge, no previous published research has evaluated a low carbohydrate diet and its influence on QoL and glycemic control in Australian adults living with T1DM. Moreover, this is the first study to develop and validate an Australian T1DM-specific QoL questionnaire Therefore, the strengths of this study are its unique approach.

The potential limitations of this study include the fact that, first, the Australian diabetes-specific QoL questionnaire is not available to those who are vision impaired, intellectually impaired, or have any other type of diabetes, such as T2DM and gestational diabetes mellitus. Future studies could develop resources to include these populations. Second, in study phases 1 and 2, questionnaire data will be self-reported and may have the potential to produce social desirability bias [73]. However, using self-reported data is the most feasible option for this pilot study in order for the sample size (N=364) and statistical validation of the questionnaire to be achieved. Third, study phase 3 has been designed as a nonrandomized intervention group pilot study that will inform the design and feasibility of a potential larger randomized control trial. Finally, in study phase 3, there is potential selection bias: individuals who are highly motivated to improve glycemic control are more likely to participate [25].

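### Table 4 plans between-person analyses of low carbohydrate diet for primary outcomes 3.1 and 3.2, but Phase 3 is one group all prescribed that diet, so the 12-week change is not what the plan estimates

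*Protocol article*

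**What the plan says.** All references are to the protocol article.

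- **Statistical Plan, Table 4.** The objective behind primary outcome 3.1 is "To examine the association between a low carbohydrate diet and glycemic control", and the one behind 3.2 is "To examine the association between quality of life and a low carbohydrate diet". In both rows the independent variable is low carbohydrate diet. The dependent variable is glycemic control or QoL, not change in either. The analysis for 3.2 is "Bivariate: ANOVA and correlations. Multivariate: hierarchical regression controlling for sociodemographic covariates"; the 3.1 row differs only by a footnote mark. Neither row names a visit factor, a change score, or a paired or repeated-measures method.
- **Intervention Procedure.** "All participants will follow a prescribed meal plan to meet their estimated energy needs", and "Meal plan macronutrient distribution will be 20% carbohydrate, 25% protein, and 55% fat".
- **Discussion.** "study phase 3 has been designed as a nonrandomized intervention group pilot study". No control group is described anywhere.
- **Abstract, Methods.** The Phase 3 primary outcomes are changes in HbA1c and QoL over 12 weeks on the diet. The pre- and postintervention sections have both measured before and after.
- **Sample Size, Phase 3.** Sixteen completers, significance level 0.05, power 0.8, for a 1.0% HbA1c difference. No SD and no test are given.
- **Study Outline, Phase 3.** The aim is pursued "through use of a cross-sectional cohort study". Study Design and Ethics also calls the whole study cross-sectional.
- **Preintervention Procedure.** Participants "complete the daily food diary 1 week prior to commencing the intervention and for the 12 weeks of the intervention". The diaries are to be used in the final analysis, but how is not said.

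**The concern.** The methods in Table 4 compare people who differ in exposure. In Phase 3 everyone is assigned the same exposure, and the only contrast the design supplies is before versus after in the same person. So the stated analysis for two of the three Phase 3 primary outcomes does not answer the question posed in the Abstract.

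If the mismatch stays, the analyst must choose the real primary analysis after data are in hand: how diet is coded, whether pairing is respected, and which covariates enter. With about 16 completers those choices can decide the result.

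**Working it through.** **1. Diet coded as assigned.** One row per person, n = 16, diet = 1 for all.
- Variance of diet = 0, so its correlation with any outcome is undefined and a one-way ANOVA has a single group.
- Intercept plus diet: 2 columns, rank 1. Adding 7 covariates: 9 columns, rank 8. The diet coefficient is not identifiable in either model.

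**2. Diet recoded as visit (pre = 0, post = 1).** 32 rows, 16 persons.
- Person indicators plus visit: 17 columns, rank 17. The before-after contrast is estimable, so the data are adequate.
- Adding 7 covariates fixed within person: 24 columns, rank still 17. Covariates such as education or diabetes duration at entry do not change the within-person contrast. Weight is an exception, because it is re-recorded after the intervention.

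**3. The plan's own figure.** N = 16 cannot be reproduced forwards, because no SD or test is stated. Solving backwards for a two-sided paired t-test (15 df, noncentrality 1.0 × √16 / SD of change, power 0.80) gives an SD of change of 1.33. This is an assumption of the check and not a protocol value.

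**4. Cost of ignoring pairing.** Per-visit SD = 1.334 / √(2(1 − ρ)), where ρ is the pre-post correlation. The true standard error of the mean change is 1.334/√16 = 0.33 whatever ρ is. The unpaired analysis uses SD × √(2/16). Power is from simulating correlated pairs (200,000 runs per row, true change 1.0%), tested by two-group ANOVA, which is equivalent to an unpaired t-test.

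| ρ | Per-visit SD | Unpaired SE | Power, unpaired | Power, paired |
|---|---|---|---|---|
| 0.5 | 1.33 | 0.47 | 0.55 | 0.80 |
| 0.7 | 1.72 | 0.61 | 0.28 | 0.80 |
| 0.8 | 2.11 | 0.75 | 0.11 | 0.80 |

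The correlated pairs must be simulated. A two-independent-samples power formula would understate the loss at the higher correlations.

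**5. Covariate load.** The questionnaire tables for Phases 1 and 2 list gender, age, height, weight, diabetes duration, occupation and education, and leave the list open. If a list like that entered a one-row-per-person model with one parameter each:
- residual df = 16 − 1 − 7 = 8, and fewer if occupation or education needs several categories;
- expected R² with no true association = p/(n − 1) = 7/15 = 0.47.

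**6. Power of the recommended analysis at 16 completers.** One-sample t on change, 1.0%, two-sided 0.05, with SD of change assumed: SD 1.0 gives 0.96; 1.2 gives 0.88; 1.4 gives 0.76; 1.5 gives 0.70; 2.0 gives 0.47.

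**The case against.** **The diet is not literally identical for everyone.** Meal plans are individualised to estimated energy needs, and intake is recorded daily. At an assumed 4 kcal per gram, 20% of 1400 to 2000 kcal is 70 to 100 g. This stands. A reader might infer that the diet effects cannot exist at all, but that is true only if diet means assignment. A diary-based intake variable would vary between persons and over time. Table 4 does not name one, however, and an intake-outcome correlation is a different quantity from a 1.0% mean change. With n = 16, only a correlation of about 0.65 is detectable with 80% power.

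**Table 4 is presented as a brief summary, and fuller detail may sit elsewhere.** ANOVA may be shorthand for repeated-measures ANOVA, and the Abstract already signals change. This is fair as far as it goes. But the point is not that detail is missing: Table 4 states variables and methods, and these do not fit the design. Even with repeated-measures ANOVA, the correlations and the covariate-adjusted regression would not estimate the mean change.

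**The covariate list belongs to the Phase 1 and 2 questionnaires.** This is correct. Table 4 does not say that all of these covariates enter a Phase 3 model, so the overfitting is conditional. A reader might also call such a model saturated, but 8 residual df is severe overfitting and not saturation.

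**The sample size does not prove that a paired test was meant.** Correct. It is tempting to say that 16 is plausible only for a paired comparison. With no SD or test stated, the protocol does not support that: a normal-approximation two-group formula with SD 1.0 also gives 16, per group.

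**Covariates can matter.** In a regression of change in outcome on change in intake, age or diabetes duration could confound. So a blanket ban on adjustment would be wrong there.

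**Conclusion.** The analysis stated for primary outcomes 3.1 and 3.2 does not fit a single group all prescribed the diet, and it does not estimate the 12-week change that the Abstract makes primary and that the 1.0% HbA1c target appears to concern. The defect is in the written plan. The pre and post measurements will exist and can support a valid analysis, so it would be wrong to conclude that Phase 3 cannot answer these objectives.

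That Table 4 names no pre-post or paired term follows directly from the text. The power loss rests on an assumed SD of change of 1.33 and on the pre-post correlation, which the protocol does not give. The overfitting rests on a covariate list like that of Phases 1 and 2 being used. The cross-sectional label is wrong for a 12-week before-after intervention, but whether it led to the choice of methods is not something the document shows.

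**What to change.** 1. In Study Design and Ethics and in Study Outline, describe Phase 3 as a single-arm pre-post study instead of cross-sectional.
2. In Table 4, make the primary analysis for 3.1 and 3.2 the mean within-person change in HbA1c and in QoL, with 95% CI, by paired t-test or a mixed model with visit and a participant random intercept. If repeated-measures ANOVA was meant, say so.
3. If an association with diet is also wanted, define the exposure as change in diary carbohydrate intake from the run-in week to the intervention weeks, related to change in outcome. Label it exploratory, and adjust for the baseline value and at most one or two prespecified covariates.
4. Drop the full sociodemographic hierarchical regression as the primary Phase 3 analysis.
5. State the test and the assumed SD of change behind N = 16, so that the sample size and the analysis can be seen to match.

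The cost is a rewording of Table 4, the design label and the sample size paragraph. No new data, visits or participants are needed.

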## Results

To date, 12 participants have been recruited into phase 1 of this study. The anticipated data collection completion date for all study phases is March 2022. At present, no study results are available.

## Discussion

This study is the first of its kind to examine the association between a low carbohydrate diet, QoL, and glycemic control. This cross-sectional study protocol aims to develop, pilot, and validate a diabetes-specific QoL questionnaire and determine if an association exists between QoL and glycemic control while using a low carbohydrate dietary intervention in Australian adults living with T1DM.

The strengths of this study are that, to our knowledge, no previous published research has evaluated a low carbohydrate diet and its influence on QoL and glycemic control in Australian adults living with T1DM. Moreover, this is the first study to develop and validate an Australian T1DM-specific QoL questionnaire Therefore, the strengths of this study are its unique approach.

The potential limitations of this study include the fact that, first, the Australian diabetes-specific QoL questionnaire is not available to those who are vision impaired, intellectually impaired, or have any other type of diabetes, such as T2DM and gestational diabetes mellitus. Future studies could develop resources to include these populations. Second, in study phases 1 and 2, questionnaire data will be self-reported and may have the potential to produce social desirability bias [73]. However, using self-reported data is the most feasible option for this pilot study in order for the sample size (N=364) and statistical validation of the questionnaire to be achieved. Third, study phase 3 has been designed as a nonrandomized intervention group pilot study that will inform the design and feasibility of a potential larger randomized control trial. Finally, in study phase 3, there is potential selection bias: individuals who are highly motivated to improve glycemic control are more likely to participate [25].

The Australian diabetes-specific QoL questionnaire will be a useful instrument for health care professionals, including general practitioners, diabetes dietitians, and diabetes educators. This instrument will support health care practitioners to gain a better understanding of Australian T1DM adults’ QoL perception relating to physical, psychological, social, and dietary well-being. To date, studies that have investigated the influence of a very low or low carbohydrate diet and glycemic control in adults living with T1DM have not examined QoL using a validated instrument in tandem with participants undertaking the dietary regimen [12,13,19,21,23-31]. Consequently, a validated QoL instrument is needed for clinical practice and future research to identify the QoL of Australian adults with T1DM, as no validated instrument currently exists.

It is recommended that people living with T1DM follow healthy eating dietary guidelines for the general population [3]. However, this study’s dietary intervention outcomes could provide an alternative approach. Additionally, the study findings could warrant the development of a specific dietary guideline for using a low carbohydrate diet to support glycemic management and improve QoL in adults living with T1DM.

This study will generate a new validated QoL instrument which could be used in evidence-based practice and research to understand the QoL of adults with T1DM. It will also investigate the association of a low carbohydrate diet, QoL, and glycemic control in Australian adults living with T1DM. If successful, this study has the potential to have a profound impact on those living with T1DM.

## Abbreviations

CDE: credentialed diabetes educator
CGMS: continuous glucose monitoring system
DQOL: Diabetes Quality of Life
GCHHS: Gold Coast Hospital and Health Service
HbA_1c_: glycated hemoglobin
MOS SF-36: Medical Outcomes Study 36-Item Short Form Health Survey
PAID: Problem Areas in Diabetes
QoL: quality of life
QR: quick response
SERTA: Study, Education and Research Trust Account
T1DM: type 1 diabetes mellitus
T2DM: type 2 diabetes mellitus
